#### 2.4.2. Cognitive Behavioural Smoking Cessation Intervention and Control App (Control Condition)

The cognitive–behavioral psychological treatment applied in this condition is identical to the one described above in the experimental condition, but with a control App (Table 1 and Table 2). This App will be used during the treatment sessions (Phase 1) and follow-up period (Phase 2), with only two basic contents: a smoking self-report tool, and access to the written materials in pdf format provided during the face-to-face sessions.

### 2.5. Procedures

One baseline assessment session will be conducted in an individual face-to-face interview using a video call. The researchers conducting the baseline assessments will be blind to group allocation, which will occur subsequently. The randomization will be performed according to a computer-generated allocation sequence (ratio: 1.1).

The cognitive–behavioral treatment will be delivered through video calls using Microsoft Teams. The smoking cessation treatment has been manualized to train the therapists and improve the intervention implementation. It includes a detailed session-by-session protocol and follow-up procedures. Study supervisors will assess fidelity by randomly visualizing treatment sessions in both arms.

Both conditions will be administered in eight weekly 60-min sessions. At the end of treatment (session 8), there will be a post-treatment assessment and face-to-face follow-ups through video calls at 3, 6, and 12 months. Trained therapists (Master level in clinical or counseling psychology) will conduct the assessment, intervention sessions, and follow-ups. 

This study was reviewed and approved by the Institutional Ethics Review Board of the University of Santiago de Compostela (USC-15/2020). The study is carried out in accordance with the Declaration of Helsinki. The potential participants will be asked to read and sign an informed consent form before any study procedures. The interested individuals will be initially screened for eligibility, and those who meet the inclusion criteria will be assessed. 

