## 2. Materials and Methods

### 2.1. Research Design

The proposed study is a two-arm, single-blind, randomized controlled trial (NCT04765813) to assess the efficacy of a cognitive–behavioral intervention for smoking cessation complemented by an App. The overall study design is summarized in Figure 1.

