### 2.6. Measures

An online face-to-face structured interview will assess sociodemographic characteristics, tobacco-related information, smoking cessation treatment history, and depression treatment history. In addition, the following instruments will be used (Table 3 lists the measures collected at each time point):-*Smoking Habit Questionnaire* [30]. This questionnaire consists of 56 items gathering information about sociodemographic variables (gender, age, marital status, educational level) and tobacco use (i.e., number of cigarettes smoked per day).-*Fagerström Test for Cigarette Dependence* (FTCD) [31,32]. This scale assesses cigarette dependence with six items. Cronbach’s alpha coefficient was 0.60 in studies conducted in Spain [33].-*Nicotine Dependence Syndrome Scale* (NDSS) [34,35]. This questionnaire assesses nicotine dependence using a multidimensional conceptualization of substance dependence. The reliability of the general factor that evaluates nicotine dependence is adequate (Cronbach’s alpha 0.80).-*Structured interview for the assessment of the DSM-5 diagnostic criteria for tobacco use disorder* [36].-*Minnesota Nicotine Withdrawal Scale* (MNWS) [37]. This 8-item scale measures nicotine withdrawal symptoms (depression, insomnia, irritability/frustration/anger, anxiety, difficulty concentrating, restlessness, increased appetite/weight gain) and craving (smoking urgency). The reliability of this instrument is good (Cronbach’s alpha 0.85).-*Self-Efficacy/Smoking Temptation Scale* [38]. This 9-items instrument assesses the temptation to smoke in different situations: positive affect/social situations, positive affect situations, and habit situations.-*Questionnaire of Urgency to Smoke* [39]. This questionnaire consists of 10 items evaluating tobacco craving. This questionnaire has two factors: (1) the intention or desire to smoke, and (2) the expectations of negative reinforcement or improvements through smoking.-*Beck Depression Inventory II* (BDI-II) [40,41]. This self-report consists of 21-items assessing depressive symptoms during the last two weeks. The reliability of this instrument is good (Cronbach’s alpha 0.90).-*EuroQoL-5D Quality of Life Questionnaire* [42]. This is a standardized and generic instrument to assess health-related quality of life. It consists of (1) assessment of five dimensions: mobility, self-care, activities of daily living, pain/discomfort, and anxiety/depression; and (2) a visual-analog scale where the individual indicates the score (ranging from 0 to 100) that best represents his/her overall health status on the day of the interview.-*Questionnaire about the use of smartphones and Apps*. This is an ad hoc questionnaire collecting information about the use of smartphones (i.e., frequency, time of use, type of use) and Apps (i.e., frequency of use, hours of use, types of Apps).-*End-of-treatment questionnaire*. This self-report collects information about quit date, confidence in remaining abstinent, perceived social support, and physical and psychological improvements since the beginning of treatment.-*Client Satisfaction Questionnaire* [43]. This 8-item instrument measures overall satisfaction with treatment services.-*Satisfaction with App questionnaire*, in which data about satisfaction and usability are collected at the end of treatment and at 3-, 6-, and 12-months follow-up.-*Follow-up questionnaire*, in which abstinence and lapse/relapse data are collected at 3-, 6-, and 12-months follow-up.

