#### 2.7.1. Primary Outcome

The primary outcome was the self-reported seven-day point prevalence of complete smoking abstinence (“not even a puff”) at 12-months follow-up. 

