Some potential limitations should be acknowledged. As noted earlier, due to the COVID-19 pandemic and resource limitations, abstinence will only be self-reported, and biochemical verification will not be performed. The biochemical verification of abstinence is desirable, as it increases scientific rigor, limiting the impact of misreporting smoking status [50]. However, the current circumstances limit the benefits of biochemical verification due to participant and staff safety, economic costs, and sample collection feasibility. Moreover, the use of video calls instead of in-person sessions might impact trial outcomes. Video calls attended at home might be perceived by some patients as being intrusive; moreover, minorities, lower-income, and older populations might have more difficulties to access virtual treatment [51]. Similar limitations may be encountered in regard to the characteristics of the users of mHealth Apps [52]. However, the strengths, such as cost-effectiveness, ease to deliver at a large scale, accessibility, and attractiveness [24], clearly overpower these limitations.

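### The plan gives treatment and the follow-up calls that collect an unverified self-reported primary outcome to one group of therapists and states no masking at follow-up, so the single-blind label gives no assurance of blind outcome assessment

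*Protocol article*

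**What the plan says.** All references are to the protocol article.

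- **Who does what.** Section 2.5: "Trained therapists (Master level in clinical or counseling psychology) will conduct the assessment, intervention sessions, and follow-ups". The same section says "there will be a post-treatment assessment and face-to-face follow-ups through video calls at 3, 6, and 12 months".
- **Where abstinence is recorded.** Section 2.6 describes the follow-up questionnaire as one "in which abstinence and lapse/relapse data are collected at 3-, 6-, and 12-months follow-up". Table 3 places the App-satisfaction questionnaire at the same three time points.
- **Primary outcome.** Section 2.7.1: "The primary outcome was the self-reported seven-day point prevalence of complete smoking abstinence", assessed at 12 months. The limitations paragraph of section 3 adds that "abstinence will only be self-reported, and biochemical verification will not be performed".
- **Blinding.** Section 2.1: "The proposed study is a two-arm, single-blind, randomized controlled trial". The Abstract uses the same label. Neither place names the blinded party. The only masking procedure is in section 2.5: "The researchers conducting the baseline assessments will be blind to group allocation, which will occur subsequently".
- **What therapists see.** In Table 1 only the experimental column has therapists introduce App usage, set reduction goals in the App and check activity compliance with its tools. The control App (section 2.4.2) holds a self-report tool and the written materials.

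**The concern.** The endpoint is what a participant says about smoking, and nothing objective stands behind it. The report is due at a live-call follow-up conducted by the staff group that delivered the treatment, and the article's main hypothesis favours one arm. Wish to please and interviewer expectation can both act on such an answer. If they act more strongly in one arm, they bias the primary comparison, and a larger sample does not remove that bias.

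With biochemical verification ruled out, masked or self-completed collection is the main inexpensive protection left, and the article provides for neither. A reader who meets the single-blind label may suppose that the outcome assessors are the blinded party. The limitations paragraph acknowledges the lack of verification but not the lack of stated masking at follow-up.

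**Working it through.** **Step 1: does any stated masking cover the primary outcome?**

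| Stage | Who, according to the article | Masking stated |
|---|---|---|
| Baseline | Researchers (also trained therapists, by the later sentence in 2.5) | Yes, before allocation |
| Eight sessions | Trained therapists | No; not possible given Table 1 |
| 3-, 6- and 12-month calls | Trained therapists | No |

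The one masked stage ends before an arm exists. It therefore cannot protect an outcome recorded a year after treatment. The article states neither separation of treating and assessing therapists nor masking at follow-up.

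**Step 2: inputs for an illustration of size.** From section 2.3: control abstinence 30%, planned difference 20 points, 99 per group, 25% attrition. The plan's inflation reproduces: 99 / (1 − 0.25) = 132 per group, 264 in total. This point disputes no sample-size figure. Section 2.3 does not state sidedness; I use a two-sided 0.05 test.

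The assumed input, which the documents do not give, is m: the extra share of continuing smokers in the experimental arm who are recorded as abstinent, with no extra share in controls.

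**Step 3: spurious gap.** With true abstinence of 30% in both arms:

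observed experimental rate p₁ = 0.30 + 0.70·m; observed control rate p₂ = 0.30; gap = 0.70·m.

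**Step 4: false-positive rate.** With n per arm and p̄ = (p₁ + p₂)/2:

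SE₀ = √[2·p̄(1 − p̄)/n], SE₁ = √[(p₁(1 − p₁) + p₂(1 − p₂))/n],

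P(reject) = Φ[(gap − 1.96·SE₀)/SE₁] + Φ[(−gap − 1.96·SE₀)/SE₁].

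For m = 10% and n = 132: p₁ = 0.37, p̄ = 0.335, SE₀ = 0.0581, SE₁ = 0.0579. The upper term is Φ[(0.070 − 0.1139)/0.0579] = Φ(−0.757) = 0.2245. The lower term is below 0.001. The sum is 0.225.

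| m (assumed) | p₁ | Gap | P(reject), 132 per arm | P(reject), 99 per arm |
|---|---|---|---|---|
| 5% | 33.5% | 3.5 points | 9.4% | 8.2% |
| 10% | 37.0% | 7.0 points | 22.5% | 18.0% |
| 15% | 40.5% | 10.5 points | 43.0% | 33.9% |

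An exact calculation for the uncorrected chi-squared test gives 9.5%, 22.6% and 43.0% at 132 per arm (5.1% with no misreporting), and 8.4%, 18.1% and 33.8% at 99 per arm.

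To create the full planned 20-point difference from nothing, m would have to be 0.20/0.70 = 28.6%.

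**Step 5: what the illustration depends on.** If misreporting occurs in both arms, the gap is 0.70·(m_E − m_C), which is zero when the shares are equal. Under a true 50% versus 30%, an equal share m in both arms shrinks the difference to (0.50 + 0.50m) − (0.30 + 0.70m) = 0.20·(1 − m), for example 18 points at m = 10%. Only the part that differs between arms inflates false positives.

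**The case against.** The other side has several good points.

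- **Same person?** A reader might infer that each participant reports abstinence to his or her own therapist. Section 2.5 does not say so. It assigns the roles to a staff category, and its labels are loose: it has researchers doing the baseline assessment in one sentence and therapists in another. What can be said is that the roles are merged and no separation is stated.
- **Is the label false?** A reader might conclude that single-blind is contradicted. It is not. The blinded party is never named, and since controls also receive an App, participant blinding is a possible reading. The label is undefined.
- **Is baseline masking useless?** No. Assessing people before allocation guards against selection at entry, which matters because eligibility requires correctly completed pre-treatment questionnaires (2.3). It does nothing for the 12-month outcome.
- **Is the pressure different by arm?** Therapist contact and follow-up schedule are the same in both arms, so much of the wish to please may cancel. One might point to a year of achievement notifications in the experimental arm, but in Phase 2 those go to abstainers; relapsers and smokers receive prompts to quit. Over-reporting that the App itself induces comes from the participant, and a masked interviewer would not remove it.
- **Does App satisfaction unmask?** Both arms have an App and Table 3 shows no restriction by arm. Answers may reveal the arm; it is not shown that they would.
- **Is this detail left to a fuller document?** Section 2.5 says the treatment manual contains follow-up procedures, and section 2.8 says data are collected in electronic format, so self-completion may already be in use. This tempers the point but does not answer it: the article says positively who conducts the follow-ups and describes masking only at baseline.

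What survives is narrower than a charge of unblinded assessment by the treating therapist, but it concerns the primary outcome.

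**Conclusion.** The concern holds in this form: as written, the plan lets therapists who know the arm of the participants they treat conduct the calls at which an unverified self-reported primary outcome is due, and it states no separation or masking there. The single-blind label gives no assurance that outcome assessment is blind.

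The size is unknown. The range of 3.5 to 10.5 points, with about 9% to 43% false positives at 132 per arm, rests on assumed extra misreporting of 5% to 15% in the experimental arm only. It should not be read as an estimate of what assessor unblinding will do, since masking the interviewer would remove only part of any such bias. It shows that modest differential misreporting would matter in a trial of this size.

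This should be changed: it is an avoidable weakness in the primary outcome with an inexpensive remedy.

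**What to change.** 1. Have the 12-month abstinence items collected in one of two ways: by an existing therapist who did not treat that participant and is not told the arm, or on a self-completed electronic form sent before the call. Section 2.3 already requires an email address.
2. Ask the abstinence items before the App-satisfaction questionnaire.
3. State in sections 2.1 and 2.5 who is blinded and who collects the 12-month outcome.
4. If outcome collection stays unblinded, say so and add it to the limitations paragraph of section 3, beside the absence of biochemical verification.

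**Cost.** Scheduling work among therapists and less continuity for participants. The article does not give the number of therapists, so the sponsor must confirm that cross-assignment is feasible; the electronic form avoids that question. Enrolment began in September 2021 (2.10), so a change may leave a mix of collection modes. Record the mode used for each participant so that the analysis can take it into account.

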### 2.6. Measures

An online face-to-face structured interview will assess sociodemographic characteristics, tobacco-related information, smoking cessation treatment history, and depression treatment history. In addition, the following instruments will be used (Table 3 lists the measures collected at each time point):-*Smoking Habit Questionnaire* [30]. This questionnaire consists of 56 items gathering information about sociodemographic variables (gender, age, marital status, educational level) and tobacco use (i.e., number of cigarettes smoked per day).-*Fagerström Test for Cigarette Dependence* (FTCD) [31,32]. This scale assesses cigarette dependence with six items. Cronbach’s alpha coefficient was 0.60 in studies conducted in Spain [33].-*Nicotine Dependence Syndrome Scale* (NDSS) [34,35]. This questionnaire assesses nicotine dependence using a multidimensional conceptualization of substance dependence. The reliability of the general factor that evaluates nicotine dependence is adequate (Cronbach’s alpha 0.80).-*Structured interview for the assessment of the DSM-5 diagnostic criteria for tobacco use disorder* [36].-*Minnesota Nicotine Withdrawal Scale* (MNWS) [37]. This 8-item scale measures nicotine withdrawal symptoms (depression, insomnia, irritability/frustration/anger, anxiety, difficulty concentrating, restlessness, increased appetite/weight gain) and craving (smoking urgency). The reliability of this instrument is good (Cronbach’s alpha 0.85).-*Self-Efficacy/Smoking Temptation Scale* [38]. This 9-items instrument assesses the temptation to smoke in different situations: positive affect/social situations, positive affect situations, and habit situations.-*Questionnaire of Urgency to Smoke* [39]. This questionnaire consists of 10 items evaluating tobacco craving. This questionnaire has two factors: (1) the intention or desire to smoke, and (2) the expectations of negative reinforcement or improvements through smoking.-*Beck Depression Inventory II* (BDI-II) [40,41]. This self-report consists of 21-items assessing depressive symptoms during the last two weeks. The reliability of this instrument is good (Cronbach’s alpha 0.90).-*EuroQoL-5D Quality of Life Questionnaire* [42]. This is a standardized and generic instrument to assess health-related quality of life. It consists of (1) assessment of five dimensions: mobility, self-care, activities of daily living, pain/discomfort, and anxiety/depression; and (2) a visual-analog scale where the individual indicates the score (ranging from 0 to 100) that best represents his/her overall health status on the day of the interview.-*Questionnaire about the use of smartphones and Apps*. This is an ad hoc questionnaire collecting information about the use of smartphones (i.e., frequency, time of use, type of use) and Apps (i.e., frequency of use, hours of use, types of Apps).-*End-of-treatment questionnaire*. This self-report collects information about quit date, confidence in remaining abstinent, perceived social support, and physical and psychological improvements since the beginning of treatment.-*Client Satisfaction Questionnaire* [43]. This 8-item instrument measures overall satisfaction with treatment services.-*Satisfaction with App questionnaire*, in which data about satisfaction and usability are collected at the end of treatment and at 3-, 6-, and 12-months follow-up.-*Follow-up questionnaire*, in which abstinence and lapse/relapse data are collected at 3-, 6-, and 12-months follow-up.

### 2.7. Outcomes

The main smoking cessation outcomes were defined based on the updated recommendations by the Society for Research on Nicotine and Tobacco (SRNT) Treatment Research Network [44].

#### 2.7.1. Primary Outcome

The primary outcome was the self-reported seven-day point prevalence of complete smoking abstinence (“not even a puff”) at 12-months follow-up. 

#### 2.7.2. Secondary Outcomes

The secondary outcomes were:

The self-reported seven-days point prevalence of complete smoking abstinence (“not even a puff”) at the end of treatment (week 8), 3-, and 6-months follow-up;

The self-reported 30-days point prevalence smoking abstinence at 3-, 6-, and 12-months follow-up;

The self-reported prolonged smoking abstinence with lapses (no more than 5 cigarettes) from the end of treatment and each follow-up point assessment at 3-, 6-, and 12-months;

The reduction by 50% or more in the number of cigarettes smoked per day from baseline to the one-year follow-up.

We will also explore the adherence, satisfaction, usability of the App, and specific tool usage in relation to smoking cessation outcomes.

### 2.8. Data Management and Confidentiality

Data will be collected from the participants in an electronic format using a unique identification code number assigned to each participant for trial documents and electronic databases. All data will be kept in password-protected computer folders at the Smoking Cessation and Addictive Disorders Unit (University of Santiago de Compostela). Only authorized trial staff will have access to trial documents.

### 2.9. Ethical Principles

This study has been designed in accordance with the Declaration of Helsinki. The Bioethics Committee of the University of Santiago de Compostela approved this study (USC-15/2020), which is registered with the international standard randomized controlled trial number, NCT04765813 (www.clinicaltrials.gov accessed on 21 February 2021). The participants will be provided with both oral and written information regarding the study before obtaining their informed consent.

### 2.10. Trial Status

The present study started participants’ enrollment in September 2021, and the recruitment is ongoing.

### 2.11. Statistical Analysis

A descriptive analysis to summarize the characteristics of the total sample will be conducted. Comparisons between the two groups will be performed using an independent sample *t*-test for continuous variables (i.e., number of cigarettes smoked per day) and a chi-squared test for categorical variables (i.e., smoking status). Logistic regression analyses adjusted for baseline characteristics (i.e., sex, age, education level) will be carried out to examine whether abstinence rates differ significantly between conditions at the end of treatment, and at 3-, 6-, and 12-months follow-up. Mediation analysis will be conducted to analyze the role of different variables (i.e., depressive symptoms) in the relationship between treatment condition and smoking status. Multilevel and survival analysis will also be carried out to examine the relapse process. All data analysis will follow the intention-to-treat principle, which includes in the primary analysis all randomized participants [45]. A *p* value < 0.05 will be considered statistically significant.

The study results will be reported following the Consolidated Standards of Reporting Randomized Trials of Social and Psychological Interventions (CONSORT-SPI 2018) statements [46,47].

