### 2.3. Participants

Sample size calculation was performed using the software developed by Wang and Ji [26]. To detect a 20% difference (50% abstinence in the experimental group vs. 30% in the control group) between conditions at the 12 months follow-up (90% power at an alpha of 0.05), a minimum of 99 participants per group will be required. With an estimated attrition of 25%, 264 participants (132 per group) are required.

To be included in the study, participants should meet the following inclusion criteria: (1) 18 years of age or older; (2) smoke at least six cigarettes per day; (3) desire to participate voluntarily in the smoking cessation treatment; (4) correctly fill out all the pre-treatment assessment questionnaires; (5) able to provide written informed consent; (6) currently own a valid email address; and (7) having a smartphone with an Internet connection (Android or iOS) and being willing to use it during treatment.

Exclusion criteria include: (1) having a diagnosis of a severe mental disorder (bipolar disorder and/or psychotic disorder); (2) having a substance use disorder (alcohol, cannabis, cocaine, heroin), different from a tobacco use disorder; (3) smoke rolling tobacco, snuff, cigars, little cigars, or other tobacco products (i.e., e-cigarettes); (4) have participated in an effective psychological treatment to quit smoking during the previous 12 months; (5) have received an effective pharmacological treatment to quit smoking in the previous 12 months (nicotine gum or patches, bupropion, varenicline); (6) have a physical pathology involving life-threatening risks for the person which would require immediate intervention in an individual format (e.g., recent myocardial infarction, pneumothorax); and (7) have a visual impairment that impedes the use of the App.

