Smoker (never quit during phase 1)	Smoking cessation tips Smoking self-monitoring tool Possibility of setting a quit date in a calendar Access to the intervention written materials in pdf format Self-recorded motivational videos List of reasons to quit tool Motivational strategies to quit Cognitive and behavioral strategies for coping with cravings Motivational notifications during the follow-up period promoting the initiation of a quit attempt	Smoking self-monitoring tool Access to the written materials in pdf format
Relapser (quit at least 24 h during phase 1)	Smoking cessation tips Smoking self-monitoring tool Possibility of setting a new quit date in a calendar Access to the intervention written materials in pdf format Self-recorded motivational videos List of reasons to quit tool Motivational strategies to initiate a new quit attempt Cognitive and behavioral strategies for coping with cravings Motivational notifications during the follow-up period promoting the initiation of a new quit attempt	Smoking self-monitoring tool Access to the written materials in pdf format

**Table 3 ijerph-19-09770-t003:** Timeline for data collection across the trial.

Measures	Measurement Time-Point				
	Baseline	End of Treatment	3-Months Follow-Up	6-Months Follow-Up	12-Months Follow-Up
Smoking Habit Questionnaire	X				
TUS Tobacco DSM-5 criteria	X				
FTCD	X	X	X	X	X
NDSS	X	X	X	X	X
MNWS	X	X	X	X	X
SSE	X	X	X	X	X
QSU	X	X	X	X	X
BDI-II	X	X	X	X	X
EQ-5D	X	X	X	X	X
APP-Q	X				
CSQ-8		X			
Satisfaction with App questionnaire		X	X	X	X
Follow-up questionnaire			X	X	X

TUS = Tobacco Use Disorder; FTCD = Fagerström Test of Cigarette Dependence; NDSS = Nicotine Dependence Syndrome Scale; MNWS = Minnesota Nicotine Withdrawal Scale; SSE = Self-Efficacy/Smoking Temptation Scale; QSU = Questionnaire of Urgency to Smoke; BDI-II = Beck Depression Inventory II; EQ-5D = EuroQoL-5D Quality of Life Questionnaire; APP-Q = Apps and Smartphone use Questionnaire; CSQ-8 = Client Satisfaction Questionnaire.

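### Section 2.11 compares the arms on continuous measures by an unadjusted t-test and leaves the collected baseline values unused, a minor loss of precision that costs nothing to avoid

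*Protocol article*

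**What the plan says.** All references are to the protocol article.

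- **Test for continuous variables.** Section 2.11 follows its descriptive sentence with comparisons between the two groups: an independent-samples t-test "for continuous variables (i.e., number of cigarettes smoked per day) and a chi-squared test for categorical variables (i.e., smoking status"). It gives no time point, covariate or change score.
- **Where adjustment appears.** Covariates are named for abstinence only: "Logistic regression analyses adjusted for baseline characteristics (i.e., sex, age, education level) will be carried out to examine whether abstinence rates differ". The covariates given as examples include no baseline value of a continuous measure. Multilevel models are tied to relapse: "survival analysis will also be carried out to examine the relapse process".
- **What is collected.** Table 3 ("Timeline for data collection across the trial") marks FTCD, NDSS, MNWS, SSE, QSU, BDI-II and EQ-5D at baseline, end of treatment, and 3, 6 and 12 months. Section 2.6 puts cigarettes per day in the Smoking Habit Questionnaire, which covers "tobacco use (i.e., number of cigarettes smoked per day") and which Table 3 marks at baseline only. A one-year value is still needed for a secondary outcome in Section 2.7.2: "The reduction by 50% or more in the number of cigarettes smoked per day from baseline to the one-year follow-up".
- **Entry conditions.** Section 2.3 requires participants to "smoke at least six cigarettes per day" and to "correctly fill out all the pre-treatment assessment questionnaires".

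**The concern.** A t-test on a follow-up value ignores what is known about the same participant at entry. Where the two values are correlated, part of the follow-up spread could be explained by baseline, and the unadjusted test leaves it in the error term. The estimated difference also moves with any chance difference between the arms at baseline.

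Here the baseline values exist and should be nearly complete, since correct completion of the pre-treatment questionnaires is an inclusion criterion. At stake are wider intervals, and a greater chance of missing a real difference, for consumption, dependence, withdrawal, temptation, craving, mood and quality of life.

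**Working it through.** **Step 1: does the sentence reach follow-up data?** Its categorical example is smoking status. Every entrant must smoke (Section 2.3), so that variable cannot differ between arms at baseline. Section 2.4.1 and Table 2 define smoking status for Phase 2, as abstinent, relapsed or smoker, which is after randomisation. Later in Section 2.11 it is the outcome of the mediation analysis. The sentence therefore covers follow-up comparisons, at least in part.

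**Step 2: does another stated analysis supply the adjustment?** No. The logistic regression is for abstinence, and the multilevel and survival models are for relapse.

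**Step 3: inputs.** The plan gives no power figure for a continuous measure, so there is none to reproduce. From Section 2.3 I take 99 analysed per arm, which agrees with 132 randomised and 25% attrition (132 × 0.75 = 99). The correlation r between baseline and follow-up is not in the document. I assume 0.3 to 0.6, with a two-sided 0.05 test.

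**Step 4: formulas.**
- Variance factor with baseline adjustment: 1 − r².
- Adjusted power at the effect for which the t-test has 80% power: Φ[(1.960 + 0.842)/√(1 − r²) − 1.960].
- Number per arm a t-test needs to match adjustment with 99: 99/(1 − r²).
- Standard error of the chance baseline difference: √(2/99) = 0.142 SD. A difference of that size moves the unadjusted contrast by r × 0.142 SD.

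Example for r = 0.5: the factor is 1 − 0.25 = 0.75, and power is Φ(2.802/0.866 − 1.960) = Φ(1.276) = 0.899.

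| Assumed r | Variance factor | Reduction | Power (t-test 80%) | t-test n per arm to match 99 | Shift from one-SE imbalance |
|---|---|---|---|---|---|
| 0.3 | 0.91 | 9% | 83.6% | 109 | 0.043 SD |
| 0.4 | 0.84 | 16% | 86.4% | 118 | 0.057 SD |
| 0.5 | 0.75 | 25% | 89.9% | 132 | 0.071 SD |
| 0.6 | 0.64 | 36% | 93.8% | 155 | 0.085 SD |

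At r = 0.1 the reduction is only 1%.

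**Step 5: cigarettes per day.** Abstainers score zero whatever they smoked before, which lowers r. I simulated a log-normal baseline with median 18, kept entrants at six or more, set 30% or 50% to zero at follow-up independently of baseline (the abstinence rates in Section 2.3), and put continuing smokers at 70% (SD 25%) of their baseline. Apart from the entry limit and the abstinence rates, these inputs are assumptions. The result depends strongly on the baseline spread:

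| Log-SD of baseline | 30% zeros: r (reduction) | 50% zeros: r (reduction) |
|---|---|---|
| 0.3 | 0.35 (12%) | 0.25 (6%) |
| 0.4 | 0.44 (19%) | 0.33 (11%) |
| 0.6 | 0.57 (32%) | 0.43 (19%) |

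The range is about 6% to 32%.

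**The case against.** Four arguments can be made for leaving the text alone.

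1. **No declared outcome is touched.** The primary outcome and all the listed secondary outcomes are binary. Abstinence has an adjusted logistic regression, and the 50% reduction outcome already uses each participant's own baseline. Section 2.7 names none of the seven scales. This stands in full. A reader might infer that the trial's efficacy conclusion is at risk, and the document does not support that.

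2. **The t-test is valid.** Under randomisation it is unbiased and keeps its 5% error rate. This also stands. A reader might infer that chance imbalance produces extra false positives. It does not, because the t-test's standard error already allows for that imbalance. The estimate is sensitive to imbalance only once a particular imbalance has occurred.

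3. **The sentence may describe baseline only.** It follows a descriptive sentence and names no time point, and the questionnaire holding cigarettes per day is marked at baseline only. This stands in part. The smoking-status example rules out a purely baseline reading, and the 50% reduction outcome needs a one-year cigarette count. The text does not, however, commit the trial to t-tests on all seven scales at every visit. Any use of the sentence on baseline variables would alter no treatment estimate and is a reporting matter.

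4. **Models for supporting scales can be left to an analysis plan.** That would answer a complaint of silence. Here a method is named, and it is the less efficient one.

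**Conclusion.** The point holds as a minor, free improvement. Section 2.11 states a valid but inefficient comparison for continuous measures that the trial also takes at baseline, and nothing else in the section makes up for it.

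The size rests on a correlation that the document does not give. Over assumed values of 0.3 to 0.6 the avoidable variance is 9% to 36%. At r = 0.5 a t-test would need 132 per arm to match adjustment with 99, a gap equal to the plan's whole attrition allowance. For cigarettes per day, the sentence's own example, the gain may be as small as about 6%, so it should not be presumed as large as for the scales. If r is near 0.1, almost nothing is lost. The imbalance figure of 0.142 SD assumes about 99 analysed per arm.

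**What to change.** In Section 2.11, for continuous measures at follow-up, replace the t-test with a linear regression of the follow-up value on arm and the baseline value of the same measure, plus the covariates already listed (sex, age, education level). Report the adjusted mean difference with its confidence interval. Use robust standard errors for cigarettes per day because of the many zeros.

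The cost is one or two sentences. It needs no new data and no extra participants. Section 2.10 says recruitment was ongoing, so the wording could be settled before outcome data are analysed.
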